### Aims

The main aims of this study are to:

1. Describe the evolution of early neurobehavioural development in infants <30 weeks from birth to two years’ CA compared with children born at term, and to explore how neurobehaviour is influenced by perinatal variables.

2. Explore the relationship between early neurobehavioural development and neonatal brain abnormalities (development and injury) at term using multi-modal MRI in infants <30 weeks at birth.

3. Investigate the predictive validity of neurobehavioural assessments during the early neonatal period for developmental outcomes at one and two years’ CA in infants <30 weeks at birth.

4. Examine symptoms of depression, anxiety, and post-traumatic stress in mothers and fathers of infants <30 weeks at birth and to describe changes in parental psychological wellbeing over the first two years of the child’s life compared with children born at term.

5. Examine parental psychological wellbeing, and parent and family factors during the neonatal period as predictors of development at one and two years’ CA in children born <30 weeks, and whether these relationships are similar in children born at term.

In addition, secondary aims of this study are to:

1. Explore whether neurobehavioural examinations in the preterm period relate to concurrent physiological status (i.e. heart rate and oxygen saturations) in infants <30 weeks at birth.

2. Describe the parenting beliefs and practices of parents of infants <30 weeks at birth across the first two years of the child’s life.

3. Examine whether parental psychological wellbeing from birth to one year CA is associated with the parent–child relationship and child development when the child is one and two years’ CA in infants <30 weeks at birth.

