### Outcomes at one and two years’ corrected age (both preterm and term infants)

At one and two years’ CA families will be contacted to participate in follow-up. The child will have a developmental assessment, both parents will be asked to participate (separately) in a parent–child interaction task, and both parents will be asked to complete a set of questionnaires.

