#### Parental assessment

Parent questionnaires will be collected at multiple time points. The first will be when their infant has their first neurobehavioural assessment. Both parents will then be asked to complete questionnaires fortnightly until term equivalent age, at term equivalent age, at three and six months, and at six-monthly intervals until the child’s second birthday (CA). The questionnaires at 3, 6 and 18 months will be posted to families, and asked to be returned to the investigators in a prepaid envelope. Parents will be sent text messages as a reminder to complete questionnaires. The term, one and two year questionnaires will be completed at the time of the infant’s follow-up assessments. Not all measures will be collected at all time points. Each questionnaire to be used in the study is described in Table 4. The time taken to complete these questionnaires will vary from 5 minutes at earlier ages to approximately 2 hours (total) at 24 months’ CA.

**Table 4 T4:** Description and purpose of parental questionnaires

**Assessment**	**Purpose**
CES-D	The *Centre for Epidemiological Studies Depression Scale (CES-D)*[62] will be used to measure depressive symptoms. The questionnaire consists of 20 questions (total score range 0 to 60) with higher scores representing greater depressive symptoms. A score ≥16 on the CES-D represents significant depressive symptoms. This threshold has been shown to correlate well with clinician ratings of depression [63]. The CES-D has been used extensively in general populations and has been used with parents of preterm infants [64,65].
HADS	The *Hospital Anxiety and Depression Scale (HADS)*[66] will be used to assess anxiety. The HADS assesses symptoms of anxiety and depression using 7 items for each scale that are scored with a 4-point rating scale (total score range 0 to 21). Scores above 11 are considered to indicate significant symptoms of depression or anxiety. The HADS has been validated in a variety of settings and has been found to perform well in assessing the severity of anxiety disorders and depression, not only in primary care patients and the general population [67] but also in parents of preterm infants [68].

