### Secondary aims

1. To explore whether the neurobehavioural trajectory varies according to concurrent physiological status, physiological status variables of interest will be dichotomised or separated into distinct categories (e.g. stable versus unstable). The mean (and 95% CI) scores at each time point (as described above) will be plotted separately for children within each category. Trends over time will be modelled using separate mixed effects regression models for each of the neurobehavioural scores including a fixed effect for time (gestational and chronological age) and physiological status and an interaction between time and physiological status to assess whether the effect of time is different in the different categories of this variable.

2. To describe the parenting beliefs and behaviour of parents of very preterm children across the first two years of the child’s life compared with term-born controls, we will present means and 95% CI for each parental assessment at each time point from term equivalent age to two years. Trends over time will be compared between the two groups using separate mixed effects regression models for each parent, with a fixed effect of time (gestational and chronological age) and group as well as an interaction between time and group. Models will also include a random effect to allow for repeated measures within a parent.

3. To examine whether parental psychological wellbeing is associated with the parent–child relationship when the child is one and two years’ CA, average scores for parental mental health from birth to 6 months, and from one to two years will be used as predictors of the 6 outcomes scales of the parent–child relationship measure at one and two years CA respectively. Separate linear regression models will be used for mothers and fathers to examine these relationships.

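### Secondary aim 3: the analysis windows do not match the aim, so first-year parental wellbeing is not tested against the two-year relationship, and the two-year predictor includes a same-visit score

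*Protocol article*

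**What the plan says.** The Aims section opens secondary aim 3 with "Examine whether parental psychological wellbeing from birth to one year CA is associated with" two things: the parent–child relationship and child development, when the child is one and two years old. One exposure window is named, and it serves both outcome ages.

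The matching analysis (Secondary aims, item 3) states that "average scores for parental mental health from birth to 6 months, and from one to two years will be used as predictors" of the six outcome scales of the parent–child "relationship measure at one and two years CA respectively". The last word fixes the pairing: birth to 6 months goes with one year, and one to two years goes with two years. No child development outcome is named there.

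On timing, Parental assessment says of the questionnaires: "Both parents will then be asked to complete questionnaires fortnightly until term equivalent age, at term equivalent age, at three and six months", then "at six-monthly intervals until the child" reaches the second birthday. It adds: "The term, one and two year questionnaires will be completed at the time of" the infant's follow-up assessments. At those same one- and two-year follow-ups, "both parents will be asked to participate (separately) in a" parent–child interaction task. Table 3 places that assessment at 12 and 24 months. Table 5 schedules CES-D and HADS at 12, 18 and 24 months, and PCL-S at term, 12 and 24 months only.

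**The concern.** The aim and its analysis define different exposures, and both are stated outright, so no further detail in an analysis plan could make both true. A two-year result from the planned model could be reported as the answer to a question about the first year that the model does not ask.

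The same-visit score adds a problem of interpretation. When part of the predictor is recorded at the visit where the outcome is observed, an association may reflect the parent's state on that day, or the child's effect on the parent, as well as any earlier influence. The one-year model does not have this feature, so the two planned models estimate different kinds of association and should not be read side by side.

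The aim also promises child development as an outcome, and the analysis of this aim does not deliver it.

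**Working it through.** The plan gives no figure on this point, so the check sets the aim, the analysis and the schedules side by side.

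**Step 1. Windows and scores (Aims; Secondary aims, item 3; Table 5).**

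| Outcome age | Window in the aim | Window in the analysis | CES-D/HADS in the analysis | PCL-S in the analysis |
|---|---|---|---|---|
| One year | birth to 12 months | birth to 6 months | birth, fortnightly, term, 3, 6 months | term |
| Two years | birth to 12 months | 12 to 24 months | 12, 18, 24 months | 12, 24 months |

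For the two-year outcome, the two windows have only the 12-month point in common. No score from birth, the fortnightly series, term, 3 months or 6 months enters that model. For the one-year outcome, the analysis stops at 6 months where the aim runs to 12.

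**Step 2. Share of the two-year predictor taken at the outcome visit.** The 24-month questionnaires and the 24-month interaction task belong to the same follow-up.
- CES-D and HADS: 1 of 3 scores = 33%.
- PCL-S: 1 of 2 scores = 50%.

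**Step 3. What the same-visit score can do.** This is an illustration only, because the document gives no correlations. Assume scores of equal variance with correlation ρ between visits. Let r be the correlation of each earlier score (12 and 18 months) with the two-year outcome, and c that of the 24-month score.
- Average of 12, 18 and 24 months: correlation with the outcome = [(2r + c)/3] / √[(3 + 6ρ)/9].
- Average of 12 and 18 months only: r / √[(2 + 2ρ)/4].
- PCL-S average of 12 and 24 months: [(r + c)/2] / √[(2 + 2ρ)/4].

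Extreme case, r = 0, with c from 0.2 to 0.3 and ρ from 0.4 to 0.7:
- smallest: (0.2/3)/√0.8 = 0.075; largest: (0.3/3)/√0.6 = 0.129;
- PCL-S: from 0.1/√0.85 = 0.108 to 0.15/√0.7 = 0.179;
- without the 24-month score: 0.

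Milder case, r = 0.2 and c = 0.3: 0.301 with the 24-month score against 0.239 without it at ρ = 0.4, and 0.261 against 0.217 at ρ = 0.7.

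So a purely concurrent association can appear as a small apparent prediction. If the earlier scores are themselves related to the outcome, the distortion is modest.

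**Step 4. Child development.** Item 3 models the six relationship scales only. The nearest substitute is main aim 5. Its analysis fits models for two-year cognitive, motor and social-emotional outcomes, and the Aims section limits its predictors to the neonatal period. Two things have no stated model: development at one year in relation to parental wellbeing, and development at either age in relation to wellbeing after the neonatal period.

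**The case against.** The strongest defence is that the aim speaks of association, and predictor can be ordinary regression vocabulary. On that reading a same-visit score is not an error in itself. This stands in part: the difficulty lies in a temporal or predictive reading, not in fitting the model. It does not rescue the window, because the aim ends the exposure at one year.

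A second defence is that following the aim literally for the one-year outcome would bring in the 12-month questionnaire, itself completed at the outcome visit. The planned six-month cut-off avoids this. That stands fully: for the one-year outcome the analysis is better than the aim, and the aim's wording should change.

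Third, main aim 5 already relates parental wellbeing to two-year development. That stands in part, within the limits shown above.

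A reader might go further and infer that the birth-to-6-month average is also contaminated: questionnaires run fortnightly to term, so parents of more immature infants contribute more of them. The document does not support this.
- It says only that scores are averaged and does not specify an unweighted mean. Weighting is commonly left to an analysis plan.
- A mean does not move merely because it contains more scores, and no bias in a coefficient has been shown.
- The fortnightly questionnaires run to term equivalent age, so scores before term are not necessarily in-hospital scores.
- PCL-S falls only once in that window, at term.

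At most, the average could usefully be defined as time-weighted.

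**Conclusion.** The point holds as a contradiction between a secondary aim and its own analysis. As written, the two-year model cannot answer the aim: it shares one time point with the intended window and draws a third of its CES-D/HADS scores, or half of its PCL-S scores, from the outcome visit. These shares assume that the one-to-two-year window includes both end points, which is its plain reading, and that all scheduled forms are returned. The window mismatch and the missing development outcome rest on the text alone. The size of any distortion from the same-visit score rests on assumed correlations and is likely to be small to moderate.

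It would be wrong to conclude that the exposure is unsound throughout. The one-year model ends its exposure before the outcome visit and is prospective. This is a secondary aim of an observational study, so the matter should be corrected, but it does not threaten the main aims.

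**What to change.** 1. **Two-year outcomes:** use the birth-to-one-year average as the exposure. Every score in it precedes the 24-month visit. Report any model that contains the 24-month score separately, labelled as a concurrent association.
2. **One-year outcomes:** keep the birth-to-6-month average and reword secondary aim 3 to say so. If the 12-month score is also of interest, report it as concurrent.
3. **Child development:** add the development outcomes at one and two years to the same models, or delete them from the aim.
4. **Optional:** state how the average is formed, for example as a time-weighted mean.

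The cost is a change of wording and a few extra regressions. All the scores are already in Tables 3 and 5, so no new data collection is needed.

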### Sample size

A sample of 150 very preterm infants and 150 term-born controls was chosen based upon projected workload, the number of infants <30 weeks cared for each year at the Royal Women’s Hospital, and the expected consent rate for the study from families. A sample of 150 infants will enable us to estimate the mean of any neurobehavioural measure employed in this research at any time point to within +/−0.16 standard deviations (based on a 2-sided 95% confidence interval, Aim 1), and to identify correlations between observations as small as 0.2 (Aims 2 and 3), with 80% power (based on 5% significance).

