### Recruitment

A research nurse will approach eligible families of very preterm children within the first or second week of life, following approval from the medical team. The research nurse will verbally explain the study, including the time commitment and give written information on the study. Both parents will be invited to be in the study. If the parent/s agree to be in the study they will be asked to sign a consent form. Families of term-born infants will be approached by a research nurse prior to discharge following the same methodology as above.

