Each examination will be video-recorded so that assessments can be scored later as appropriate. As infants prior to term age in the NICU can be sensitive to handling we will not administer any item considered to cause the infant unnecessary stress. During the assessment, we will simultaneously observe pulse oximetry data, which will give information on oxygen saturations and heart rate. If these data and other behaviour, such as apnoea, suggest increased stress levels in the infant as a result of the neurobehavioural assessment, administration of that item will cease. The assessment will be continued where possible. Due to the poor self-regulation abilities and sensitivity to handling of infants younger than 30 weeks’ GA, it will be necessary for early evaluations (<30 weeks’ GA) to principally involve observation, focusing on: GMs [40], state, motor and autonomic regulation and the infant’s response to external stimuli. Behavioural (e.g. colour changes, facial expressions) and motor observations (e.g. postural tone and quality of spontaneous movements) will be video-recorded during a standard care procedure (e.g. a nappy change) to evaluate the infant’s response to handling during an everyday activity. The video recordings will allow the assessor to make more detailed assessments than they are able to do in real-time and allow for inter-observer reliability of scoring (two scorers will be used to assess reliability). Evaluations will be completed weekly from enrolment up to 32 weeks’ GA, then fortnightly until term, or discharge from the Royal Women’s Hospital. Assessments will be timed to coincide with care procedures to ensure the infants’ sleeping patterns are not disrupted. Initially assessments will take approximately 15 minutes and increase to 30 minutes as the infants become older and more stable, enabling us to elicit more specific responses.

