#### Magnetic resonance

The MRI scan is not a compulsory component of the study and parents consenting to the study can choose for their baby not to have the MRI scan. For those who consent, MRI scans will be performed without anaesthesia or sedation, between 38–44 weeks’ GA on the same day as the term equivalent age neurobehavioural assessment. All scans will be performed at the Royal Children’s Hospital using the 3 T Siemens Magnetom Trio MRI scanner. The scanning session will take approximately 60 minutes. A full anatomic, functional, developmental and metabolic infant brain MRI study will be performed using the following sequences:

•**T2-weighted images:** Transverse Restore turbo spin echo imaging: Flip angle = 120, Repetition Time = 8910 ms, Echo Time = 152 ms, Field Of View = 192 × 192 mm, Matrix = 192 × 192, 1 mm [3] isotropic voxels.

•**T1-weighted images:** Transverse multi-planar reconstruction imaging with noise suppression: Flip angle = 9°, Repetition Time = 2100 ms, Echo Time = 3.39 ms, Field Of View = 192 × 192 mm, Matrix = 192 × 192, 1.0 mm [3] isotropic voxels.

•**Diffusion weighted imaging:** Transverse echo planar imaging: Repetition Time = 20400 ms, Echo Time =120 ms, Field Of View =173 × 173 mm, Matrix = 144 × 144, 1.2 mm [3] isotropic voxels, 45 gradient directions (range b = 100 to b = 1200s/mm [2]), 3 b = 0 s/mm [2].

•**Resting state functional connectivity MRI:** Transverse 2D echo planar imaging with prospective acquisition correction: Repetition Time = 2910 ms, Echo Time = 28 ms, flip angle = 90°, Field Of View = 151 × 151 mm, Matrix = 64 × 64, 2.4 mm [3] isotropic voxels.

•**Proton magnetic resonance spectroscopy:** Transverse spin echo chemical shift imaging: Repetition Time = 2000, Echo Time = 135, flip angle = 90°, scan resolution = 12 × 12, interpolated 16 × 16, field of view = 103 × 125 mm, voxel size = 10.4 × 8.6 × 15.0 mm.

The MRI scans will be qualitatively evaluated by two independent investigators who are blinded to the clinical neurobehavioural assessment, utilising an established scoring method for newborn infants [42]. This scoring system provides an overall measure of the presence and severity of white matter, cortical grey matter, deep grey matter and cerebellar abnormalities (recorded as normal, mild, moderate, or severe). Quantitative image analysis will involve the following image analyses:

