#### Data collection & analysis

The data will be analysed according to the following main aims:

1. To describe the longitudinal evolution of early neurobehavioural development in very preterm infants (<30 weeks’ GA), from birth to two years CA the mean and 95% confidence intervals (CI) for the neurobehavioural assessment will be presented by week up to 32 weeks’ gestation, then fortnightly from 32 weeks’ gestation to term equivalent age, as well as at 1 and 2 years corrected age. Data will be presented according to both gestational and chronological age. Trends over time (according to both chronological and gestational age) will be explored using a mixed effects regression model for each outcome fitted to the continuous age measurement with a fixed effect of time (age) and a random effect for individuals to allow for the repeated observations on each infant.

2. To explore whether the neurobehavioural trajectory varies according to MR findings at term, qualitative MRI variables of interest will be dichotomised into two distinct categories (moderate to severe vs. none or mild white matter injury). The mean (and 95% CI) scores for the neurobehavioural development outcomes at each time point (as described for aim 1) will be plotted separately for children within each category. The change in neurobehavioural development over time (according to both chronological and gestational age) will be modelled using separate mixed effect regression models for each of the neurodevelopmental scores with a fixed effect of time (age) an indicator for moderate-severe injury and an interaction between time and the injury indicator, to assess whether the effect of time is different in those with a moderate-severe injury compared with those with no or a mild injury. The association between early neurobehavioural development and quantitative MRI (e.g. volumes, diffusion, metabolites such as NAA and cho) will be analysed using linear (continuous outcomes) and logistic (binary impairment outcomes) fitting a separate regression model for each outcome and neurobehaviour time point (according to both chronological and gestational age).

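### The stated precision of ±0.16 SD at any time point holds only where all 150 preterm infants contribute, which the entry rules exclude for the early gestational weeks and discharge makes unlikely late before term

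*Protocol article*

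**What the plan says.** The Sample size section of the protocol article gives the number of infants, "A sample of 150 very preterm infants and 150 term-born controls was chosen", and then two properties of the 150 preterm infants. The first is the precision of a mean: "A sample of 150 infants will enable us to estimate the mean of any neurobehavioural measure employed in this research at any time point". The half-width is given as ±0.16 SD, for a two-sided 95% interval. The second is power for associations: "to identify correlations between observations as small as 0.2 (Aims 2 and 3), with 80% power (based on 5% significance".

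Other sections fix who can be observed and when:

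- **Inclusion criteria for preterm infants:** birth at any gestation below 30 weeks.
- **Recruitment:** families are approached "within the first or second week of life, following approval from the medical team".
- **Serial neurobehavioural assessments up to term:** assessment is weekly from enrolment to 32 weeks, "then fortnightly until term, or discharge from the Royal" hospital.
- **Data collection & analysis, Aim 1:** "the mean and 95% confidence intervals (CI) for the neurobehavioural assessment will be presented by week up to 32 weeks", then by fortnight to term, and at one and two years, on both gestational and chronological age. Trends use a mixed model with age as the fixed effect and a random effect for the infant.
- **Magnetic resonance:** "The MRI scan is not a compulsory component of the study".

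**The concern.** The precision is promised without qualification for every time point, while the schedule lets infants join the gestational-age axis at different weeks and leave it at discharge. The number behind each weekly mean must therefore vary, and it is smallest at the start. The Background and Discussion present the period before term, and before 32 weeks in particular, as the study's main gap to fill. The precision is overstated most in the earliest of those weeks.

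The composition of the raw means changes as well. Early gestational weeks can hold only the most immature infants, and late pre-term visits hold only those still in hospital. A curve of raw means by gestational age then mixes maturation with gestation at birth and length of stay. A reader using it as a norm could take a change in who is observed for a change in development.

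The correlation figure for Aims 2 and 3 comes from the same 150 infants, although Aim 2 needs an optional scan and Aim 3 needs follow-up to one and two years.

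**Working it through.** **Inputs from the documents.** There are 150 preterm infants, with a two-sided 95% confidence interval and a stated half-width of 0.16 SD. The stated detectable correlation is 0.2 at 80% power and 5% significance (Sample size). The entry and exit rules are those listed above.

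**Step 1: reproduce the stated precision.** In SD units the half-width is 1.96/√n.

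- n = 150: 1.96/12.247 = 0.160. With the t distribution (149 df) it is 0.161.
- Inverted: (1.96/0.16)² ≈ 150.

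The figure is arithmetically right and uses every infant. On the normal formula it no longer rounds to 0.16 once n is 141 or fewer.

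**Step 2: can all 150 be present?**

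- *Early gestational weeks:* no. An infant born at 29 weeks cannot supply a value at 25 to 28 weeks, and an infant not yet enrolled supplies none. This follows from the design and is not attrition.
- *Fortnightly visits from 32 weeks to term:* unlikely once discharges begin, because discharge ends the in-hospital series. The article gives no discharge timing.
- *Term, one year and two years:* possible in principle, but only with no losses.

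**Step 3: half-width for smaller numbers.** The n values are assumptions.

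| n observed | share of 150 | half-width (SD) |
|---|---|---|
| 150 | 100% | 0.160 |
| 120 | 80% | 0.179 |
| 75 | 50% | 0.226 |
| 50 | 33% | 0.277 |
| 25 | 17% | 0.392 |

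As an illustration only, suppose births are spread evenly over completed weeks 24 to 29 (150/6 = 25 per week) and enrolment comes one week after birth. Then n at 25, 26, 27 and 28 weeks is 25, 50, 75 and 100, and the half-widths are 0.39, 0.28, 0.23 and 0.20 SD. If births lean towards later weeks, the earliest means are less precise; n = 15 would give 0.51 SD.

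**Step 4: the correlation figure.** By Fisher's transformation, detectable r = tanh[(1.960 + 0.842)/√(n − 3)] for a two-sided 5% test with 80% power.

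- n = 150: tanh(2.802/12.124) = tanh(0.2311) = 0.227.
- n = 135 (90% followed up, assumed): 0.239.
- n = 120 (80% scanned, assumed): 0.253.
- n = 50 (an early week, assumed): 0.387. This case arises because Aim 3 and the quantitative MRI part of Aim 2 fit a separate model for each neurobehavioural time point.

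At n = 150 the power for r = 0.2 is about 69%, and about 194 infants would be needed for 80%. A one-sided 5% test gives a detectable r of 0.202, but the article does not say the test is one-sided.

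**Step 5: the trend model.** The mixed model uses all available observations, but its stated terms are age and a random effect for the infant. Gestational age at birth, which decides which early ages an infant can contribute, is not among them. The weekly means and intervals are not adjusted at all.

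**The case against.** The strongest reply is that the arithmetic is correct and only the scope of a few words is too wide. The sample size was set by workload, admissions and consent rate, so ±0.16 SD did not determine it. Each mean will be published with its interval, so the real precision will be visible. Data are also shown by chronological age, where late birth does not keep an infant out of the early weeks after enrolment. The mixed model uses every observation, and Aim 1 already intends to explore perinatal variables.

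Most of this stands as a limit on the point. The impossibility belongs to the gestational-age axis, and nothing here shows that the study is too small. It does not rescue a precision stated for any time point, because gestational age is one of the two axes on which the means are promised.

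Four stronger readings are tempting and are not supported:

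- *That the MRI opt-out weakens the ±0.16 SD.* It removes no infant from a neurobehavioural mean and bears only on the Aim 2 associations.
- *That ±0.16 SD fails at every time point.* The term assessment is scheduled separately from the in-hospital series, and all 150 infants could be seen there and at one and two years.
- *That the early half-widths lie in a known range, such as 0.20 to 0.40 SD.* The article gives no gestation distribution, and a later-skewed one would exceed that range.
- *That missing scans or follow-up explain the whole correlation shortfall.* Of the gap from 0.200 to 0.253 at n = 120, 0.027 of 0.053 is present at the full 150. To 0.239 at n = 135, it is 0.027 of 0.039.

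**Conclusion.** The point holds in limited form. ±0.16 SD is right where all 150 preterm infants contribute and wrong as a promise for any time point. It cannot be met on the gestational-age axis before all infants are born and enrolled. It will probably not be met at the later pre-term fortnights, and from term onwards it depends on full retention. The half-width rises to 0.23 SD if half the infants are observed and to 0.39 SD with 25. How many are observed in a given week is an assumption that the documents cannot settle.

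The detectable correlation is about 0.23 even with complete data on a two-sided test. It rounds to the printed 0.2 at one decimal, but power for a true 0.2 is about 69%, not 80%. The changing composition of the raw means follows from the entry and exit rules; the planned mixed model answers it only in part.

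**What to change.** 1. In Sample size, restate the precision as ±0.16 SD where all 150 infants contribute. Add the expected n and half-width for the earlier gestational weeks and the late pre-term visits, taken from the hospital's own distribution of gestation at birth and discharge timing.
2. Restate the detectable correlation as about 0.23 at n = 150, two-sided 5%, 80% power. Give the larger values for the expected MRI and follow-up numbers, for example 0.25 at 120 and 0.24 at 135 if those are the numbers expected.
3. In Aim 1, show n beside each raw mean and add gestational age at birth to the gestational-age mixed model. A main curve standardised to the cohort's gestation distribution is optional.

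The cost is some rewording, less favourable stated figures and one covariate that is already collected (Perinatal data collection). No further infants or assessments are needed.
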